#### Usual care group

As per the standard BSS process (see Fig. 2), individuals in the usual care group will receive an invitation to take part in BSS 2 weeks after receiving the pre-invitation letter (and study information envelope). The BSS invitation letter includes details of an assigned appointment date and time (8 weeks in advance). The letter also requests confirmation of the appointment. If no confirmation is received from the patient within 2 weeks of the invitation going out, a reminder invitation letter is sent. If confirmation is still not received within 2 weeks of the reminder, a ‘cancellation’ letter is sent and there is no further contact from the Screening Centre. If confirmation is received, an enema with preparation instructions is sent approximately 2 weeks before the appointment date. Patients who confirm but then fail to attend their appointment receive a ‘did not attend (DNA)’ letter.

#### Intervention group

Individuals in the intervention group will also follow the above usual care process. However, if an individual either fails to confirm or attend a confirmed appointment (‘non-attenders’), they will, in addition to the cancellation/DNA letter, enter a navigation episode, whereby a SSP trained in PN will make up to three attempts to contact the individual by telephone. All call attempts will be documented and, if contact is made, the SSP will establish the reasons for non-attendance, offer support and, if suitable, arrange a new appointment. The navigation episode could involve multiple telephone conversations and closes when a decision to arrange a new BSS appointment, or not, is made. Participants in the PN group will only be eligible for one navigation episode, i.e. if a further BSS appointment is made following PN, but is not attended, only a further ‘DNA’ letter is sent, as per standard practice: no additional navigation call attempts will be made.

All consenting participants will be sent an ESQ, with a freepost-return envelope, either 4 weeks following an attended appointment or 1 week after a non-attended appointment or final PN call (see Fig. 3). There will be four versions of the ESQ with questions varying depending on the participant’s study group and BSS attendance status. The aim of the ESQ is to assess participants’ knowledge of BSS and their satisfaction with their choice to attend screening or not. The ESQ for those receiving PN also aims to find out how participants felt about this process (e.g. their perceptions of the usefulness of PN and how it made them feel) and the effect PN has on various psychosocial variables such as informed choice and BSS knowledge [28–36]. If ESQs are not returned within 2 weeks, a reminder ESQ with a freepost-return envelope will be sent.

**Fig. 3 Fig3:**
[figure not shown]
Flowchart of study materials

Additionally, at the end of the study, qualitative interviews will be conducted with the SSPs, to allow an evaluation of the barriers and facilitators for implementing PN at the organisational level, exploring how PN affected SSP’s workload and processes in the wider department.

### Sample size

Currently, there is no directly comparable evidence to estimate the number of people who will consent to take part in this study. Because our sample is likely to consist of people who support the BSS in principle, we have used recruitment figures from the UK FS trial as a guide to estimating our recruitment rate.

South of Tyne Screening Centre will invite approximately 960 people for BSS at STDH during the recruitment period. In the UK FS trial, 55 % of those initially approached were interested in receiving a FS examination [37]. Given that people in this study will receive an invitation for BSS regardless of their response to our invitation, recruitment may be lower (i.e. 40 %; *N* = 384).

It is likely that uptake among this self-selected sample would be higher than for the general population. On the basis of the UK FS trial, we predict that about 70 % of the sample would attend their original appointment as part of the usual pathway. The remaining 30 % of consenting participants would fail to attend their appointment (*N* = 116) of whom we would allocate two thirds (*N* = 77) to receive PN.

Using A’Hern single-stage design, with 20 % significance level and 80 % power, at least 35 participants would need to re-schedule and subsequently attend their appointment for PN to be considered worthy of further investigation [24].

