**Methods/design:**

All individuals invited for BSS at South Tyneside NHS Foundation Trust during the 6-month recruitment period will be invited to take part in the study. Consenting participants will be randomised to receive PN or usual care in a 2:1 ratio. PN involves non-attenders receiving a phone call from a Specialist Screening Practitioner (SSP) who will elicit reasons for non-attendance and offer educational, practical, and emotional support as needed. If requested by the patient, another appointment for BSS will then be arranged. We anticipate 30 % of participants will be non-attenders. Using A’Hern single-stage design, with 20 % significance level and 80 % power, at least 35 participants who receive PN need to subsequently attend for PN to be considered worthy of further investigation in a definitive trial. The primary outcome measure will be the number of participants in the PN group who re-book and attend their BSS appointment. A qualitative analysis of the PN transcripts, and interviews with the SSPs, will also be conducted, alongside a quantitative analysis of completed patient-reported experience questionnaires. An economic analysis will calculate the costs of delivering PN.

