### Trial status

Data collection is ongoing but the randomisation ratio has now been increased to 4:1 in favour of the intervention, following lower than expected consenting rates within the first 3 months of recruitment.

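### The go/no-go threshold of 35 attenders carries its stated error rates only at the forecast 77 people, and it was not revisited when consent and the allocation ratio changed

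*Protocol article*

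**What the plan says.** The Sample size section of the protocol article builds the number for PN from a chain of forecasts. It starts from "South of Tyne Screening Centre will invite approximately 960 people for BSS at STDH during the recruitment period". It takes 40% consent (384 people), 30% of those failing to attend (116) and two thirds of these allocated to PN (77). On consent it concedes that "there is no directly comparable evidence to estimate the number of people who will consent to take part in this study".

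The rule follows directly: "Using A’Hern single-stage design, with 20 % significance level and 80 % power", then "at least 35 participants would need to re-schedule and subsequently attend their appointment for PN to be considered worthy of further investigation". The Abstract repeats it as "at least 35 participants who receive PN need to subsequently attend for PN to be considered worthy". The primary outcome under Outcome measures is also a count: PN-group non-attenders who are navigated and then attend a new appointment. Neither p0 nor p1 is stated.

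Recruitment and setting fixes a 6-month recruitment window; no stopping point at 77 non-attenders is given. Trial status then reports that "the randomisation ratio has now been increased to 4:1 in favour of the intervention, following lower than expected consenting rates". The expected number for PN and the threshold are not restated there or elsewhere. Planned analyses describes recruitment and uptake rates by arm and does not link the threshold to the number achieved.

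**The concern.** An A'Hern design is a pair: a sample size n and a cutoff r. The cutoff has its error rates only at its own n. Here r is fixed at 35, while n is whatever a fixed recruitment window, an uncertain consent rate, an uncertain attendance rate and the allocation ratio produce. Two of those inputs have changed since planning.

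If n falls short, 35 attenders is a higher proportion than the design intended, and PN may be judged unworthy because few people consented. If n overshoots, 35 is a lower proportion and an uninteresting result can pass. In either case the go/no-go reading would partly reflect recruitment rather than PN.

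**Working it through.** **Inputs from the protocol article.** 960 invited, 40% consent, 30% non-attendance, 2:1 allocation later changed to 4:1, r = 35, significance 20%, power 80%.

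**Planned n.** 960 × 0.40 = 384. 384 × 0.30 = 115.2 (the article gives 116). 115.2 × 2/3 = 76.8, or 77 as stated.

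**Reproducing 77/35.** With X ~ Binomial(n, p), alpha = P(X ≥ 35 | n, p0) and power = P(X ≥ 35 | n, p1). At n = 77, alpha ≤ 0.20 requires p0 ≤ 0.401 and power ≥ 0.80 requires p1 ≥ 0.496. Among pairs on a 5-point grid, only 40% vs 50% has n = 77, r = 35 as its smallest exact design:
- P(X ≥ 35 | 77, 0.40) = 0.194
- P(X ≥ 35 | 77, 0.50) = 0.819

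This pair is an inference, used below as an assumption.

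**n after the ratio change.** Assume half of the invitations fall under 2:1 and half under 4:1, with the same consent rate c throughout. Then n = 480 × c × 0.30 × (2/3 + 0.80) = 211.2c. The observed c is not reported, so a range is shown.

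**Keeping 35 (p0 = 0.40, p1 = 0.50 assumed).**

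| Scenario | n | 35/n | alpha | power |
|---|---|---|---|---|
| 30% consent, all 2:1 | 58 | 60% | 0.001 | 0.07 |
| 30% consent, half and half | 63 | 56% | 0.009 | 0.23 |
| 35% consent, half and half | 74 | 47% | 0.12 | 0.72 |
| one fewer than plan | 76 | 46% | 0.168 | 0.789 |
| plan | 77 | 45% | 0.194 | 0.819 |
| one more than plan | 78 | 45% | 0.222 | 0.846 |
| 40% consent, half and half | 84 | 42% | 0.42 | 0.95 |

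Under this pair, n = 77 is the only value that meets both limits.

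**Offset from 4:1.** Setting 211.2c = 77 gives c = 0.365. At about 36.5% consent, half and half, n is back at 77.

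**Sensitivity to the unstated rates.** Values of n at which 35 keeps alpha ≤ 0.20 and power ≥ 0.80:
- 40% vs 50%: 77 only
- 35% vs 50%: 77 to 87
- 40% vs 55%: 70 to 77
- 40% vs 60%: 63 to 77

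n = 58 lies outside all four ranges.

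**Chance variation alone.** Suppose 384 people consent and each is a PN-arm non-attender with probability 0.30 × 2/3 = 0.20. Averaging over n ~ Binomial(384, 0.20), the fixed 35 gives alpha 0.234 and power 0.742 under 40% vs 50%.

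**The case against.** Several points on the other side stand.

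- **p0 and p1 are inferred.** With a wider gap the fixed 35 survives some drift, so the claim that only 77 works is specific to 40% vs 50%. That pair is the likeliest reading, but it is still an assumption.
- **A reader might infer from Trial status that the rule has already failed.** The documents do not support this. The move to 4:1 was a response to low consent and pushes n back towards 77. The observed consent rate is not given.
- **A reader might infer that both error rates fail together.** For a given n under 40% vs 50%, only one does: power below 77, alpha above it. The reported change in consent is downward, where alpha is conservative, so inflated alpha is the less likely problem. Planned consent with 4:1 throughout (n = 92, alpha 0.69) is ruled out by Trial status itself.
- **A highly effective intervention could still pass.** At n = 63, a true attendance rate of 60% reaches 35 with probability 0.80.
- **35 is not the only feasibility criterion.** The Background also lists recruitment rates and acceptability to patients and staff. It is the only numerical threshold.
- **77 stands in the paragraph just before the rule, and an analysis plan not shown may re-derive the cutoff.** The first is true, and so 35 of 77 can be read. But the article itself commits to the count with named error rates, repeats it in the Abstract, and reports changed inputs without qualifying it. The point is about what is stated, not about missing detail.

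**Conclusion.** The concern holds in this form: the only numerical go/no-go rule is a fixed count whose stated 20% and 80% apply to a forecast n, and the inputs to that forecast changed without the rule being revisited.

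The size depends on the realised n and on the unstated rates. Under the assumed 40% vs 50%, a fall in consent from 40% to 30% cuts power from 82% to about 23% with the mixed ratio. At 35% consent the loss is moderate (72%). Under wider gaps the loss can be small for modest shortfalls. The main risk is a wrong no-go caused by recruitment.

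The denominator is also unsettled. Sample size counts non-attenders allocated to PN, while the Abstract counts those who receive it and Outcome measures those who are navigated. With up to three call attempts per person (Intervention group section), fewer may be reached than allocated.

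**What to change.** 1. State p0 and p1 behind the A'Hern calculation.
2. Choose one denominator, either all PN-arm non-attenders or those actually navigated, and use it in the Abstract, Sample size and Outcome measures.
3. Replace the fixed 35 with the smallest r for which P(X ≥ r | realised n, p0) ≤ 0.20, fixed before outcomes are examined. If p0 = 0.40:

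| n | 42 | 58 | 63 | 77 | 84 | 92 |
|---|---|---|---|---|---|---|
| r | 20 | 27 | 29 | 35 | 38 | 42 |

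4. Report the power at p1 for the realised n. If p1 = 0.50, it is about 68% at n = 42, 74% at n = 58 and 78% at n = 63.
5. Restate the expected n under the mixed 2:1 and 4:1 allocation and the observed consent rate.

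The cost is a paragraph and a short table, with no extra participants. The downside is a less favourable stated power if n falls short: indexing the cutoff restores control of alpha and recovers much of the power, but not all of it.

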### Outcome measures

The primary outcome measure of this study will be the number of non-attenders in the PN group who are navigated and then re-book and attend their new BSS appointment.

Additional outcomes measures will include the following:Barriers to BSS attendance: All PN sessions will be audio recorded (with patient permission) and transcribed. An analysis of the transcripts will aim to highlight all the barriers to attendance described by patients and the extent to which they are modifiable.An evaluation of the PN process: Approximately seven SSPs will be assigned to this study. SSPs will monitor the number of contact attempts made and the duration of telephone calls made within each navigation episode. The audio recordings of the navigation calls will also be analysed with regard to the SSPs adherence to the PN manual, the type of support given (e.g. practical and/or emotional), and the action plans agreed with patients. Exit interviews with SSPs will be conducted, audio recorded and analysed with the aim of ascertaining their views on the PN process. Exit interviews will either be conducted face-to-face within the hospital setting or over the telephone, whichever is most convenient for each SSP.Patient-reported outcomes: Completed ESQs will be analysed to ascertain the number of people making an informed choice in both groups and, where relevant, satisfaction with the BSS procedure and PN intervention.Reasons for not participating in the study: A brief freepost-return A5 postcard will be provided within the study invitation envelope that will be sent alongside the BSS pre-invitation letter. The postcard will give those not wanting to take part in the study the option to choose among reasons for non-response/refusal (e.g. ‘I do not want to share my personal details with the researchers’, ‘I did not think I will need any support’), with responses considered in the development of the RCT.Economic analysis: We will calculate the cost of delivering the PN intervention, including SSP time, and training. We will also plan the economic evaluation that would accompany the full RCT.

### Planned analyses

#### Primary analysis

The overall recruitment and uptake rates by trial arm will be described; the study is not powered to make a direct comparison between arms but will help inform sample size requirements for a phase III trial.

#### Qualitative analysis

Transcripts of the PN telephone calls and interviews with SSPs will be analysed separately and managed using QSR International’s NVivo 10 Software. Framework analysis will be applied to the PN telephone call transcripts, with aspects such as the barriers highlighted, advice given, and outcomes achieved extracted for review [38]. SSP interviews will be analysed using thematic analysis with an inductive approach as we aim to gain insight into the views of SSPs with regard to the intervention’s concept and design, and their experience of intervention delivery [39]. One member of the research team will lead the analysis with a further two research team members involved in discussions to verify the results. A sub-sample of anonymised transcripts will be read by our patient representative to check interpretations by the main research team. The telephone transcripts will also be matched to the corresponding SSP interview transcript to give context to the interviews and triangulate the data.

#### Quantitative analysis

Data collected on the study database and from returned non-participation postcards will be analysed and mainly reported as descriptive data (e.g. attendance rates, time for return of ESQs, number of people selecting specific reasons for non-study participation). The ESQ data will be analysed using a mixture of descriptive and inferential statistics including chi-square analysis and linear and logistic regression so that predictors of attendance and non-attendance can be investigated, as can between group differences in views, attitudes, knowledge and satisfaction with BSS. Results will be presented with a 95 % confidence interval.

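### Questionnaire answers collected after the appointment cannot show which knowledge, attitudes or satisfaction levels came before attendance, yet the plan models them as predictors of it

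*Protocol article*

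**What the plan says.** The Quantitative analysis section names the data source and the purpose. "The ESQ data will be analysed using a mixture of descriptive and inferential statistics", including "linear and logistic regression so that predictors of attendance and non-attendance can be investigated".

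The Intervention group section fixes when the questionnaire is sent: "either 4 weeks following an attended appointment or 1 week after a non-attended appointment or final PN call". It also fixes its form: "There will be four versions of the ESQ with questions varying depending on the participant’s study group and BSS attendance status". On content, "The aim of the ESQ is to assess participants’ knowledge of BSS and their satisfaction with their choice to attend screening or not". For navigated participants it also covers their view of the process and "the effect PN has on various psychosocial variables such as informed choice and BSS knowledge". A reminder is planned for questionnaires not returned, so some non-return is expected.

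The Procedure section lists what goes out with the pre-invitation letter: an information sheet, a consent form, a reply envelope and a card for people who decline. The article describes no questionnaire completed before the appointment.

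**The concern.** A predictor of attendance has to be in place before attendance is decided. Here the candidate variables are asked about afterwards, and attendance itself sets both the waiting time and the version. Having the examination can teach a person about it, and satisfaction with a choice can only exist once the choice is made. A regression of attendance on such answers can return a clear association whichever way the influence ran.

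At stake is how one secondary analysis is read. If knowledge or satisfaction is reported as predicting attendance, a reader may take it as something to change in order to raise uptake, when it may be a result of having been screened.

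**Working it through.** **1. The passages side by side**

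| Feature | Attended original appointment | Missed or did not confirm |
|---|---|---|
| ESQ sent | 4 weeks after | 1 week after, or 1 week after the final navigation call |
| ESQ version | attender version for the group | non-attender version for the group |
| Measured before the appointment | no questionnaire described | no questionnaire described |

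Two things follow. An item asked only of attenders, or only of non-attenders, cannot enter a model of attendance, because the outcome does not vary among those who answered it. For shared items, version and timing move with the outcome. Adding version as a covariate does not help: with four versions defined by group and attendance, version predicts attendance perfectly.

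**2. What the regression can estimate**

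Take a score with SD 1 in each attendance group, and let the observed mean difference (attenders minus non-attenders) be d. Then

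d = a + c + t,

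where a is the difference already present before the appointment, c is the change caused by attending or not attending, and t is the effect of different timing and version. For a normal score with equal SDs, Bayes' rule gives

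log odds(attend | x) = constant + d·x,

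so the odds ratio per SD is exp(d). Only the sum d is observed. A predictor claim needs a, and one equation cannot yield three unknowns without a measurement before the appointment.

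**3. Illustration of size**

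Inputs from the Sample size section: 960 invited × 0.40 = 384 consenters, of whom 70% attend. That gives 384 × 0.70 = 268.8 attenders and 384 × 0.30 = 115.2 non-attenders (the article states 116).

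Assumptions, not from the documents: a = 0 and t = 0, so the whole difference is a consequence of attending; c = 0, 0.2, 0.3 or 0.5 SD; return either complete, or 70% of attenders and 40% of non-attenders.

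By formula, exp(0.2) = 1.22, exp(0.3) = 1.35 and exp(0.5) = 1.65. A simulation with 1,000 runs per setting agrees:

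| c (SD) | OR, full return | Runs with p < 0.05 | OR, 70%/40% return | Runs with p < 0.05 |
|---|---|---|---|---|
| 0 | 1.00 | 5% | 1.00 | 4% |
| 0.2 | 1.23 | 46% | 1.22 | 22% |
| 0.3 | 1.36 | 79% | 1.35 | 43% |
| 0.5 | 1.65 | 99% | 1.67 | 86% |

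Return that depends on attendance alone leaves the odds ratio about where it was and lowers the chance of significance. If return also depended on the score, the odds ratio would shift too, by an amount the documents give no means of judging. The Trial status section reports consent below expectation, so the real sample may be smaller than 384. That would reduce the significance rates but would not move the odds ratios.

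**4. Where the problem does not reach**

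Sex and original appointment date do not change with attendance. Models using them are free of this problem, except that fitting them only to ESQ returners would add differential return.

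**The case against.** The strongest reply has four parts.

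*This is a small clause in a condensed article.* The analysis is exploratory, covariate lists normally sit in an analysis plan that is not shown, and predictor is often used loosely for any regression covariate. This stands as a limit on importance. It does not remove the point, because the article itself fixes the source, timing and versions of the data. An analysis plan could restrict the covariates or relabel the results, which is the change asked for, but it could not recover the missing earlier measurement.

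*The direction of the bias is not known.* This stands. A reader might infer that the models would estimate only reverse effects. The documents do not support that: the association may reflect prior differences, consequences, or both. The simulation assumes an effect of attending and shows no bias when that effect is zero.

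*Not every ESQ variable need postdate the outcome.* This stands. A reader might infer that all of them do and that no predictor can be identified. The items are not shown, and a fixed characteristic remains fixed whenever it is recorded. For a navigated participant who re-books, the wording leaves open whether the ESQ comes before the second appointment, although the original non-attendance is already known by then.

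*The barrier work rests on other data.* This stands. A reader might infer that the findings on barriers, or the decision on a definitive trial, would be distorted. The Outcome measures section takes barriers from recorded navigation calls, the Qualitative analysis section applies framework analysis to them, and no section says that the ESQ regressions feed the trial decision.

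**Conclusion.** The point holds for ESQ content that can change: knowledge, attitudes, satisfaction and informed choice. As the article describes the data, regressions of attendance on these answers cannot separate prior influences from consequences of attending or from differences in timing and version, and they cover only ESQ returners. Fixed characteristics are outside the point, apart from differential return.

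The documents allow no estimate of size. Odds ratios of 1.2 to 1.65 arise if attending shifts a score by 0.2 to 0.5 SD and there was no difference beforehand. These are assumed values and show what could happen, not what will.

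This is a secondary analysis. The primary outcome, the rule of at least 35 attenders and the transcript-based analysis of barriers are unaffected.

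**What to change.** Restrict models described as predicting attendance to variables that are fixed before the appointment and held for every consenter, and fit them to all consenters, not only ESQ returners. The article supports sex (the randomisation lists are separate by gender) and original appointment date (a study database item). Area deprivation is not among the database items listed in the Procedure section, so use it only if records can supply it. Do not use confirmation status: the Intervention group section counts failure to confirm as non-attendance, so it is part of the outcome.

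Report ESQ variables by attendance status as associations measured after the appointment, stating the 4-week and 1-week intervals and the version differences, and do not call them predictors.

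The cost is a change of analysis wording and a shorter list of predictors. No change to data collection is needed.

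### A study-arm test of satisfaction with the BSS procedure compares attenders only, and PN is designed to change who attends, so it can show a difference without any effect on satisfaction

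*Protocol article*

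**What the plan says.** The Quantitative analysis section of the protocol article applies chi-square tests and linear and logistic regression to the ESQ data, with 95% confidence intervals. One stated purpose is to examine "between group differences in views, attitudes, knowledge and satisfaction with BSS".

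Other sections show who can supply a satisfaction score:

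- Outcome measures lists, among the patient-reported outcomes, "where relevant, satisfaction with the BSS procedure and PN intervention".
- The Intervention group section describes "four versions of the ESQ with questions varying depending on the participant’s study group and BSS attendance status", and gives as one aim of the questionnaire to assess "their satisfaction with their choice to attend screening or not".

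Attendance can be changed after randomisation, in one arm only. The primary outcome is "the number of non-attenders in the PN group who are navigated and then re-book and attend their new BSS appointment". Under Usual care group, a person who still has not confirmed after the reminder is treated differently: "a ‘cancellation’ letter is sent and there is no further contact from the Screening Centre". A person who confirms and then misses the appointment is described as receiving a did-not-attend letter.

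**The concern.** Somebody who never had the flexible sigmoidoscopy cannot rate it, so an arm comparison of procedure satisfaction is a comparison among attenders. Attendance happens after randomisation, and PN exists to alter it. PN-arm attenders are a mixture of people who came to their first appointment and people who came only after navigation. Usual-care attenders consist almost entirely of the first kind. The arms compared are therefore no longer alike by design. This is separate from questionnaire non-response and would remain at 100% return.

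A difference between the two kinds of attender is plausible. The Background section lists fear of the test, difficulty with the enema instructions and fatalistic attitudes among the barriers to screening. If people who first stayed away rate the test lower, PN would appear to reduce satisfaction with BSS; if they rate it higher, PN would appear to raise it. At stake is a misleading secondary result in a study meant to shape the definitive trial.

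**Working it through.** **1. The plan's own figures (Sample size section).** The starting point is "South of Tyne Screening Centre will invite approximately 960 people for BSS at STDH during the recruitment period". With 40% consenting, 960 × 0.40 = 384. With 30% not attending, 384 × 0.30 = 115.2, which the article takes as 116. Two thirds of 116 is 77.3, taken as 77. The threshold of 35 attenders among 77 also reproduces. The article does not state the two A'Hern proportions, but with inferred values of 0.40 and 0.50 the smallest exact binomial design is 77 with a cut-off of 35 (one-sided alpha 0.194, power 0.819). No sample size is stated for satisfaction, so there is none to reproduce.

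**2. Who would be in the comparison at 2:1.**

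- Usual care: 384 × 1/3 = 128 randomised; 128 × 0.70 = 89.6 attend.
- PN: 384 × 2/3 = 256 randomised; 256 × 0.70 = 179.2 attend the first appointment and 76.8 do not.
- Navigated attenders at the threshold: 76.8 × 35/77 = 34.9.
- PN-arm attenders in all: 179.2 + 34.9 = 214.1.
- Navigated share: w = 34.9 / 214.1 = 16.3%.

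**3. Size of the artefact.** Suppose PN changes nobody's satisfaction. The expected arm difference among attenders is then w × (satisfaction of navigated attenders − satisfaction of first-appointment attenders). The documents give no satisfaction figures, so the gap is an assumption, as is the 90% satisfied among first-appointment attenders used for the last column. That column is the chance of a significant result in the direction of the artefact, in a two-sided 5% test of 214 against 90 attenders. It would be 2.5% with no artefact.

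| Assumed gap (points) | Artefact (points) | Chance of significance |
|---|---|---|
| 0 | 0 | 2.5% |
| 10 | 0.163 × 10 = 1.6 | about 6% |
| 20 | 0.163 × 20 = 3.3 | about 11% |
| 30 | 0.163 × 30 = 4.9 | not computed |
| 40 | 0.163 × 40 = 6.5 | about 30% |

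For a continuous score, a gap of 0.25, 0.5 or 1 SD gives an artefact of 0.04, 0.08 or 0.16 SD.

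**4. Sensitivity.** With only 15 navigated attenders, w = 15 / 194.2 = 7.7%. If every PN-arm non-attender were navigated into attending, w = 76.8 / 256 = 30%. The potential distortion thus grows as PN succeeds.

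Trial status reports a change to 4:1. If that ratio applied throughout, the PN arm would have 307.2 people, with 215.0 first-appointment and 41.9 navigated attenders. Then w = 41.9 / 256.9 = 16.3%, unchanged, because the mix within the PN arm does not depend on the ratio. Usual-care attenders fall to 76.8 × 0.70 = 53.8, and the chances of significance for gaps of 10, 20 and 40 points become about 5%, 8% and 19%.

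**5. Set against sampling error.** At 90% satisfied and full return, the 95% half-width for the arm difference is 1.96 × √(0.09 × (1/214 + 1/90)) = 7.4 points at 2:1. At 4:1 it is 1.96 × √(0.09 × (1/257 + 1/54)) = 8.8 points. All the artefacts in the table lie inside these widths.

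**The case against.** **The contrast is partly inferred.** The Quantitative analysis section defines neither its groups nor satisfaction with BSS. The groups could be attenders and non-attenders, and the satisfaction meant could be "satisfaction with their choice to attend screening or not", which everyone can report. The phrase in "where relevant, satisfaction with the BSS procedure and PN intervention" already hints at subgroup reporting, since satisfaction with PN cannot be compared across arms. This stands as a limit: the point holds on one reading. That reading is the natural one, because the article elsewhere uses group for trial arm and attendance status for the other split, and the same sentence handles attendance separately through its predictors.

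**The article disclaims arm comparisons, and detail belongs in an analysis plan.** The Design section says a direct comparison of arms is not the aim, and Primary analysis says the study is not powered for one. Those statements concern uptake and recruitment, and they do not withdraw the inferential comparison stated for the questionnaire. A condensed article may leave analysis populations to a fuller document; the point here is the comparison it does state.

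**The difference need not be called spurious.** Satisfaction among all attenders, under a service with PN and one without, is a legitimate descriptive quantity. That is fair. The artefact arises only if the difference is read as an effect of PN on people's satisfaction.

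**Usual care may have some re-attenders.** The article rules out further contact for non-confirmers, but does not say whether people who confirmed and then missed can rebook. So the claim is few or no counterparts, rather than none.

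**Stronger readings that the documents do not support.** A reader might infer that the comparison will show a false PN effect. It can; sign and size rest on a gap the documents do not give, and with no gap there is no artefact. A reader might also infer that the feasibility judgement is compromised. The Background names acceptability of PN to patients as the criterion, not satisfaction with the test, and perceptions of PN are asked of those who received it, without an arm contrast. Nor does the point reach knowledge, views or satisfaction with choice, which attenders and non-attenders can both report.

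**Conclusion.** The concern holds in a limited form. Read as an arm comparison that includes procedure satisfaction, the planned test conditions on attendance, which PN is designed to change, and a complete questionnaire return does not repair this. The 16% share follows from the article's 70% first-appointment attendance and its threshold of 35 in 77. The 1.6 to 4.9 points follow from that share and from assumed gaps of 10 to 30 points. At these sizes the artefact is smaller than the sampling error and unlikely to reach significance. It affects one secondary item and leaves the 35-attender rule untouched. It is worth correcting because the contrast can tell the reader little: first-appointment attenders receive no navigation in either arm, so any systematic arm difference comes essentially from the navigated attenders, and the test cannot separate a change in satisfaction from a change in who attended.

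**What to change.** In the Quantitative analysis section, take satisfaction with the BSS procedure out of the PN-versus-usual-care tests. Report it descriptively, with 95% confidence intervals, by route to attendance: first-appointment attenders (arms pooled, since neither was navigated), navigated attenders, and any usual-care participants who attended after first missing or not confirming. Limit arm comparisons of satisfaction to "satisfaction with their choice to attend screening or not", which is defined for everyone randomised, though still open to questionnaire non-response.

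The cost is a small change of wording. The Procedure section already has the study database record the original appointment, later changes and attendance, so no new data are needed. Two things are given up. There is no arm-level test of procedure satisfaction, and the navigated group is imprecise: with 35 people and an assumed 80% satisfied, the 95% half-width is 1.96 × √(0.80 × 0.20 / 35) = 13 points.
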